### Data management

Data will be entered on paper case report forms at site, staff will be trained in good clinical practice and study-specific procedures. Clinical data will then be entered manually into a SQL database by the trial administrator. Study management data will be entered into an MS Access database by the trial administrator. Both clinical and study management data will be checked visually on receipt by the trial administrator, automatic validation checks will be completed during clinical data entry (built into the SQL database) and 10% of all data manually entered into the SQL database will be checked by the data manager; finally, data will be checked during data cleaning using SPSS Syntax for validations and missing data. Only the core trial team members will have access to hard copies of the data, and these will be stored in a locked cupboard. The same individuals will have access to the study management database and the SQL database, which will both be password-protected. A data management plan will be completed and adhered to.

### Statistical methods

#### Main analysis

This protocol paper follows SPIRIT guidelines, and the analysis and reporting of this pragmatic randomised trial will be in accordance with CONSORT guidelines. Data will be analysed using the intention-to-treat principle; all eligible randomised participants will be included in the analysis. The primary comparative analyses will employ an ANCOVA model to the CEQ score (adjusting for baseline CEQ score) to investigate intervention effect at 12 months. Additional covariates included are those balanced at randomisation (type of carer and age of looked-after children in household). Although ANCOVA is robust against normality violation [19, 20], homoscedasticity will be explored using various diagnostic plots of the residuals of the fitted model (such as kernel density estimators and quantiles of the residuals against quantiles of normal distribution). If there is evidence of heteroscedasticity amongst the residuals then robust standard errors will be used. Mixed-effects three-level regression models will be used to adjust for site (local authority or independent fostering providers) as a stratification variable and to allow for clustering by block in the intervention group. The result will be presented as the (adjusted) difference in mean CEQ score between the intervention and control groups, along with 95% confidence interval and *p* value, with due emphasis placed on confidence intervals for the between-arm comparisons. A secondary analysis of the primary outcome will examine CEQ score over time incorporating the 3 month response.

Secondary outcome measures will be analysed using multilevel linear or logistic regression at 3 and 12 months follow-up. Baseline reported scores, and variables balanced at randomisation will be controlled for as covariates. Various hierarchies will be investigated to explore clustering. Repeated measures models will include an interaction term for time and trial arm to investigate any divergent or convergent pattern in outcome measures [21]. The adjusted regression coefficients will be provided alongside 95% confidence intervals and *p* values. The categorical version of SDQ total difficulties will be compared between trial arms by fitting a multilevel ordinal regression model to the SDQ category at 3 and 12 months follow-up. Baseline reported SDQ score, and variables balanced on at randomisation will be controlled for as covariates.

With validated scales, the outcome will be used as directed in the manuals, using either categorical (using validated cut-offs) or continuous score. Newly derived or modified measures will be further validated using Cronbach’s α to assess the scale reliability; a factor analysis will determine factor loadings.

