### Sample size estimation

The sample size was informed by the reported Carer Efficacy Scale results from the previous trial [12]. Based on a mean [18] score of 27.1 (3.9) in the control group, and a 2:1 ratio (intervention: control) to maximise the number of carers attending each training programme, a sample size of 213 carers (142:71) would provide 80% power at the 5% level to detect a difference of 1.6 points on the Carer Efficacy Scale. To allow for 10% loss to follow-up (owing to non-response), the sample size is inflated to 237 (158:79 respectively). Participants will be recruited at an average rate of 14 per month for 17 months (although it is recognised that recruitment will be termly in nature). This sample size is based on a maximum of one carer being recruited per household. This does not prevent two carers from the same family attending the training sessions but only one would be a trial participant. Households will be asked to identify the primary carer for the purposes of evaluation in such circumstances.

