#### Randomisation; sequence generation

Carers agreeing to participate will be allocated to a trial arm with an assignment ratio 2:1 (intervention to control group) using an algorithm that will minimise by type of carer (kin carer or unrelated carer) and age of looked-after children in the household (<12 or ≥ 12 years) for each site.

Following initial site set-up, participants may be recruited at any time-point before the first Fostering Changes group is due to commence. Allocation will only occur within 6 weeks of the start of the Fostering Changes programme and will be conducted centrally by the core trial team via telephone following notification of recruitment. There will be complete concealment of the preceding allocations from the field recruitment staff, eliminating the possibility of predicting the next allocation. Participants will be telephoned by the trial manager and informed of their allocation. With the exception of the trial manager and study administrator, all trial team members and field recruitment staff will be blinded to allocation. The trial statisticians will be unblinded after introduction of the allocation by nature of the 2:1 allocation ratio. Control-allocated carers will be able to access training after end of study period.

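### The plots named for checking homoscedasticity assess normality, so the rule that triggers robust standard errors for the primary outcome is likely to miss moderate unequal variance between arms allocated 2:1

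*Protocol article*

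**What the plan says.** All the relevant text is in the Main analysis section of the protocol article, unless another section is named.

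- **Primary model.** "The primary comparative analyses will employ an ANCOVA model to the CEQ score (adjusting for baseline CEQ score"), with the minimisation factors as further covariates. Three-level mixed models adjust for site and are meant "to allow for clustering by block in the intervention group".
- **Normality.** It is set aside at the start of the sentence on diagnostics: "Although ANCOVA is robust against normality violation".
- **Homoscedasticity.** The same sentence goes on: "homoscedasticity will be explored using various diagnostic plots of the residuals of the fitted model (such as kernel density estimators" and, as the second example, "quantiles of the residuals against quantiles of normal distribution").
- **Consequence.** "If there is evidence of heteroscedasticity amongst the residuals then robust standard errors will be used".
- **Allocation.** Under Randomisation; sequence generation, carers are "allocated to a trial arm with an assignment ratio 2:1 (intervention to control group").
- **Variability.** Sample size estimation gives a single SD: "Based on a mean [18] score of 27.1 (3.9) in the control group". No SD is given for the intervention arm.

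**The concern.** A kernel density estimate and a normal quantile plot of the residuals both describe the shape of one pooled distribution. They address normality, which the sentence has just treated as unimportant. Constant variance is a different question: does the spread of the residuals change with the fitted value or baseline score, or differ between arms? No display that answers it is named, so the examples do not serve the stated aim.

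This matters because the standard error of the primary estimate depends on the outcome of the check. In a trial with equal arms, a pooled variance would do little harm. With twice as many carers in one arm, the common variance is weighted towards the larger arm, while the true standard error is driven mostly by the smaller one. If the arms differ in spread and the check does not show it, the primary confidence interval has the wrong width, in a direction set by which arm is more variable.

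**Working it through.** **Inputs.** From Sample size estimation: 142 intervention and 71 control carers analysed, SD 3.9, difference 1.6, 5% level, 80% power. The level is taken as two-sided, which reproduces the plan's figure. Assumed, because the documents give nothing: ratios of the two arm SDs of 1.2 and 1.5 in each direction, extended to 2 in the simulation.

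**1. The plan's own figure.** For SD 3.9 in both arms, the t-based formula at 2:1 gives 70.6 controls, so 71 and 213 in total, with power 0.802. Dividing by 0.9 gives 213/0.9 = 236.7, so 237. The stated sample size reproduces and is not in question.

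**2. Standard error under a common variance.** Write sI and sC for the arm SDs.

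- Model SE² = [(142·sI² + 71·sC²)/213] × (1/142 + 1/71)
- True SE² = sI²/142 + sC²/71
- At exactly 2:1 the ratio of model to true SE² simplifies to (2sI² + sC²)/(sI² + 2sC²). It equals 1 only when the SDs are equal.
- Two-sided type I error = 2[1 − Φ(1.96 × model SE/true SE)]

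Worked example with sI = 4.68 (1.2 × 3.9) and sC = 3.9:

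- pooled variance = (142 × 21.90 + 71 × 15.21)/213 = 19.67
- model SE = √(19.67 × 0.02113) = 0.645
- true SE = √(21.90/142 + 15.21/71) = 0.607
- 1.96 × 0.645/0.607 = 2.08, so the type I error is 3.7%

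| More variable arm | SD ratio | Model SE | True SE | Type I error |
|---|---|---|---|---|
| Neither | 1.0 | 0.567 | 0.567 | 5.0% |
| Intervention | 1.2 | 0.645 | 0.607 | 3.7% |
| Intervention | 1.5 | 0.768 | 0.675 | 2.6% |
| Control | 1.2 | 0.607 | 0.645 | 6.5% |
| Control | 1.5 | 0.675 | 0.768 | 8.5% |

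The less variable arm is set to 3.9 in each row. The type I error depends only on the ratio.

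**3. Power when the intervention arm is more variable.** Power ≈ Φ(1.6/true SE − 1.96 × SE used/true SE).

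- Ratio 1.2: Φ(2.64 − 2.08) = 71% with the model SE, against Φ(2.64 − 1.96) = 75% with the correct SE.
- Ratio 1.5: Φ(2.37 − 2.23) = 56%, against Φ(2.37 − 1.96) = 66%.

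The loss due to the wrong SE is thus about 4 and 10 percentage points. The rest of the fall from 80% comes from the larger variance itself.

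**4. Would a normality-type check notice?** ANCOVA with one baseline covariate was simulated under the null at 142:71, with 10,000 replicates per scenario. A Shapiro-Wilk test on the pooled residuals stood in for reading the named plots, and Levene's test by arm stood in for a spread check. HC3 is a robust standard error with a small-sample correction.

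| More variable arm | SD ratio | Normality check flags | Spread-by-arm check flags | Type I error: model SE | Type I error: robust SE only if normality check flags | Type I error: HC3 always |
|---|---|---|---|---|---|---|
| Control | 1.25 | 7% | 50% | 7.0% | 6.8% | 4.8% |
| Control | 1.5 | 19% | 95% | 8.8% | 8.2% | 5.4% |
| Control | 2 | 71% | 100% | 10.9% | 6.4% | 4.7% |
| Intervention | 1.25 | 6% | 50% | 3.3% | 3.3% | 4.6% |
| Intervention | 1.5 | 11% | 95% | 2.7% | 2.9% | 5.1% |
| Intervention | 2 | 33% | 100% | 1.6% | 2.6% | 4.7% |

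With equal variances both checks flag about 5% of trials. For ratios up to 1.5, the normality-type trigger therefore leaves the error rate almost where the uncorrected model puts it.

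**The case against.** Several points on the other side stand.

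- **The list is open.** The plots are given only as examples, and the trigger sentence is not confined to them. Plots of residuals against fitted values or by arm are already permitted, and the article promises a full SAP before any analysis. A reader might infer that the rule is bound to miss unequal variance. The text does not support that. It supports only that a check relying on the named plots is likely to miss moderate differences. At a ratio of 2, the pooled residuals become heavy-tailed enough for a normality check to flag 33% to 71% of trials.
- **Training-group variation is already modelled.** A reader might argue that variances must differ because only one arm attends groups. The planned block effect in the intervention arm takes up that component. What remains is variation between carers in their response to training, for which the article gives no figure.
- **Direction.** A reader might take an inflated type I error as the main consequence. Variable response to training would make the intervention arm the more variable one, and the test is then conservative. Nothing in the article suggests a more variable control arm.
- **The calculations simplify.** The SD ratios are assumed, the closed form omits covariates and clustering, the simulation omits clustering, and formal tests stand in for visual reading.

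What does not stand is treating this as detail left to the SAP. The article chose to name diagnostics, and both are for a different assumption. A SAP that carries the sentence forward carries the mismatch with it.

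**Conclusion.** The point holds as a misstated diagnostic: density and quantile plots are offered as checks of constant variance, and the choice of standard error for the primary estimate depends on that check. The consequence is conditional on the arms really differing in spread, which the documents neither show nor exclude. If they do, by an assumed ratio of 1.2 to 1.5, the nominal 5% test would run at about 3.7% to 2.6% with a more variable intervention arm (the likelier direction if response to training varies between carers) and at about 6.5% to 8.5% with a more variable control arm. These figures ignore covariates and clustering. Severity is minor to moderate, and the stated sample size does not change.

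**What to change.** Either of two changes in the SAP would do.

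- **Minimum.** Name residuals against fitted values and residual spread by arm as the homoscedasticity checks, and keep the density and quantile plots for normality only.
- **Better.** Fit the primary mixed model with a separate residual variance for each arm from the outset, keeping the planned block random effect in the intervention arm. The standard error then no longer depends on how someone reads a plot. This goes beyond correcting the wording, but it removes the problem rather than improving its detection.

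The cost is one or two sentences of text. The second option adds one variance parameter, with negligible loss of precision if the variances turn out equal. Neither option affects recruitment or data collection.

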#### Subgroup and interim analysis

There is no planned interim analysis. Exploratory subgroup analyses are planned for:Age, sex, placement history of the index foster childExperience, qualifications of the foster carer and size of household

Appropriate interaction terms will be entered into the primary regression analysis to conduct pre-specified subgroup analyses. Subgroups will be fully defined in advance of any analysis being started with input from the trial team and summaries of current evidence from the literature. Since the trial is powered to detect overall differences between the groups rather than interactions of this kind, the results of these exploratory analyses will be presented using confidence intervals. A full statistical analysis plan will be completed and signed off prior to any analysis being undertaken.

### Data monitoring

Regular monitoring will be performed by the trial or data manager according to the principles of good clinical practice. Data will be evaluated for compliance with the protocol and accuracy. Following written standard operating procedures, the monitors will verify that the trial is conducted and data are generated, documented and reported in compliance with the protocol. There is no separate data monitoring committee for the trial. Any key data queries will be taken to the trial steering committee.

### Adverse event monitoring

There are no expected adverse events related to the intervention or research procedures, and the Cardiff University School of Social Sciences (SOCSI) Research Ethics Committee have approved that they should not be reported for this trial.

### Auditing

No independent audits are planned.

### Ethical and governance approval

Ethical approval for this trial was given by Cardiff University SOCSI Research Ethics Committee on 4 June 2015, reference number SREC/1515; this was centralised ethical approval for all sites. A trial steering committee will meet approximately every 6 months to provide study oversight. The trial steering committee comprises two independent academic social workers (one of whom is the chair), an independent statistician and a lay representative. The Fostering Changes programme was selected for use in the Confidence in Care project following input from a multi-sector advisory group, which included representation from heads of children’s services in Wales.

### Confidentiality

All data will be kept for 15 years, in line with Cardiff University’s Research Governance Framework Regulations for clinical research. Electronic data will be stored confidentially on password-protected servers maintained on the Cardiff University Network. All hard copy forms will be stored in locked filing cabinets. For participant interviews, all audio files will be recorded on encrypted audio-recorders and securely held in password-controlled databases on Cardiff University servers. Audio files will be transcribed and anonymised using university-approved transcription companies. No identifiable data will be published.

### Access to data

The chief investigator will have access to the final trial dataset.

### Dissemination policy

A publication plan and dissemination policy will be written. The trial results will be disseminated in full and with a lay summary on the Centre for Trials Research website, and a summary of the results will be disseminated to all participants. It is expected that all study management team members (protocol paper co-authors) will co-author the main results paper. Any data requests should be made to the Centre for Trials Research, which is a signatory of AllTrials and aims to make its research data available wherever possible.

### Process evaluation

An integral process evaluation of this complex training intervention will aid interpretation of the trial results. The process evaluation will mainly be undertaken through qualitative interviews with foster carers, training facilitators and other stakeholders. We will aim to triangulate the qualitative data on experiences of the intervention with quantitative data on attendance throughout the 12 week intervention. This is likely to include exploration of programme enrolment, quality of engagement, retention and reach.

The process evaluation will take part in two phases. The first phase will involve further development of the logic model of the intervention. The theoretical underpinnings of the training have already been proposed and, along with the initial Briskman et al. [12] trial, there is some evidence for how theoretical change mechanisms may lead to effect (hence, the selection of carer efficacy as primary trial outcome measure). Nevertheless, an explicit logical model has yet to be developed. A detailed understanding of the mechanisms of the intervention is necessary for us to explore whether the Fostering Changes programme was delivered as originally intended. The logic model will be developed through review of programme materials and refined through interaction with intervention designers. In addition, it is expected that there may be some variation in support routinely provided to carers throughout Wales. To better understand the nature of the comparison being made in the trial and how the study setting may influence outcomes, the first phase will also include an assessment of usual support for foster carers. We will use a mixed-methods approach to combine documentary analysis of key existing documents, qualitative data from interviews with foster carers and quantitative questionnaire data with foster carers about other support accessed.

Using qualitative interviews with foster carers (*n* ≤ 40), interviews with Fostering Changes facilitators and training providers (*n* ≤ 15), and quantitative measurements (including attendance rates), the second phase of the process evaluation (Table 2) will explore:

**Table 2 Tab2:** Summary of key process evaluation components (phase 2)

Component	Set-up work	Within-trial baseline, outcome assessment	Routine data collection (group training)	Exit interviews (after 12 month follow-up): carers or training providers
Fidelity	Y		Y	Y
Contamination			Y	Y
Assessing usual care	Y	Y	Y	Y
Acceptability				Y
Feasibility				Y

Fidelity of the intervention: We will develop intervention fidelity measures and assess whether the Fostering Changes programme was delivered as originally intended (e.g., quantify session attendance, qualitatively explore facilitator approach to delivery of manualised programme content) [22] and, therefore, determine whether the trial represents a good test of the intervention. We will explore barriers to, and facilitators of, optimal implementation.Acceptability of the intervention: We will explore the acceptability of the training intervention to carers; in particular, how the new elements of the programme (follow-up carer support) were experienced by carers.Feasibility of intervention implementation: This will include assessing factors that may impact implementation of Fostering Changes through interviews with training providers and other key stakeholders (e.g., leads from local authority fostering teams).Contamination within trial: We will monitor using group session attendance records and participant follow-up questionnaires and through process evaluation interview exposure of control group participants to the intervention.

Interview schedules (and where relevant, topic guides) will be developed by the research team informed by the research aims and are likely to be semi-structured in nature to allow for developing and emerging issues to be probed. Audio files of interviews will be securely held in password-controlled databases on Cardiff University servers. Digitally recorded interviews will be transcribed verbatim, anonymised using university-approved transcription procedures and checked by the researcher. No identifiable data will be published.

### Process evaluation analysis

Interview data will be subject to thematic analysis. Thematic analysis is an interpretive process, in which data are systematically searched for patterns to provide an illuminating description of the phenomenon [23]. This will involve the following stages: familiarisation with data, generating initial codes, searching, reviewing and defining themes [24]. Areas of contrast in participant perspectives, as well as similarity, will be identified. Qualitative coding software (such as NVivo10) will be used to assist in data analysis. Measures will be put into place to ensure validity and reliability. More than one researcher will be involved in the development of the coding framework and identification of themes (at global, organising and basic levels) [25]. Double coding will be carried out on a sample of the data until consensus is reached. Quantitative data on training session attendance gathered by facilitators and control group participant reports of usual care in follow-up assessment will inform sampling for qualitative interviews and be used as the basis for triangulation of collected data. An analysis plan for the process evaluation will be finalised prior to inception of the data collection.

